**Fig. 4 Fig4:**
[figure not shown]
CD-DIET Visit components3.Tissue Transglutaminase IgA Antibody Assay-TTG IgA – we anticipate that if subjects are adherent, serology will normalize or decrease with subjects randomized to the GFD and remain elevated for subjects randomized to the GCD. Blood sample will be taken from both groups at visits 3 and 5.

### Subjective measures of assessment

The subjective measures in the dietary assessments include (Fig. 3):Comprehensive dietary interviews to also include 3 day food records (at visits 1, 3 and 5) and a typical day recall (at visits 2, 4) (Fig. 1). In the absence of a 3 day food record a typical day recall will be taken. Through the records, the dietitian will assess for the presence of dietary gluten and/or hidden sources of gluten.Ranking: At the end of every dietary interview a global ranking of adherence will be applied by the dietitian. A ranking of ‘expectations’ will be applied to the subjects on the GFD arm. The ranking will range from ‘Below Expectations’ - minimal understanding of GFD concepts and inability to distinguish carbohydrate containing foods, to ‘Meeting Expectations’ – with the GFD and ability carb count, and ‘Above Expectations’ – advanced understanding of the GFD, seeks out additional information about GF carb sources and demonstrates an interest in the curriculum. A ranking of gluten inclusion and exclusion will be applied to the GCD arm. The ranking will range from “Complete inclusion of gluten containing (GC) foods to ‘Some restriction of GC foods’ to a ‘strict restriction of GC foods’.Subject’s own self report: Subjects will also have an opportunity to evaluate their own adherence with the diet that they have been randomized to from ‘strict’ to ‘partial’ to ‘none’ adherent.

## CD-DIET study dietary overview: methods and design

Subjects aged 8 to 45 years old with established T1D and biopsy confirmed asymptomatic CD will be randomized to treatment with GFD for one year or continue with their usual GCD as described (Refer to Figs. 2 and 4) [27].

### Dietitian visits

All subjects on both arms of the study will have five visits with a trained dietitian. Worksheets specific to each arm and visit have been designed to ensure consistent collection of information, and uniform parameters for assessment and education. All worksheets will be filled out by the dietitian at every visit. All participants will fill out food records (two weekdays and 1 weekend day) for visits 1, 3 and 5 (at initial assessment, 6 month and 12 months). Food records will be sent to ESHA, and will be reviewed with the participants at their following visit (visits 2 and 4, 3 and 9 months, respectively). Glycemic Index (GI) and Glycemic load (GL) will be calculated to describe the dietary carbohydrates of each arm using glucose as a reference. GI of mixed meals per day will be ranked as: Low GI ≤55, Medium GI 56–69 and High GI ≥70. Similarly GL per day will be ranked as: Low GL <80, Medium GL 80–120 and a high GL >120 [32]. Dietary gluten evaluation will be performed by using the Osborne formula for all subjects at baseline. Twenty ppm will be applied to the GFD arm as per Health Canada’s definition of GF claims.

A typical day intake is incorporated into the dietary interview at visits 2 and 4 (3 and 9 month visit respectively). All records will be assessed for dietary exclusion or inclusion of gluten. At visits 2–5 (3,6,9, and 12 months) inclusive all participants will complete with the dietitian a 'self-report' questionnaire designed to assess their comfort (both groups) and understanding of their assigned diet.

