### Dietary assignment in a clinical trial: opportunities and challenges

Symptomatic patients who follow a GFD experience an improvement in symptoms and therefore following a GFD is meaningful. However it is less clear if there are any related benefits to asymptomatic CD patients with T1D who follow a GFD. The CD-DIET Study represents an opportunity to evaluate the impact of a GFD on asymptomatic patients with CD. This is a randomized, controlled, multicenter, dietary intervention study in pediatric and adult diabetes centers across Ontario, Canada, that is based on an intention to treat. The study consists of a comprehensive dietary interview with defined subjective and objective parameters. It is designed to address the educational and psychosocial needs and challenges of living and thriving with both conditions: CD and T1D.

CD-DIET is designed to evaluate the efficacy and safety of the gluten-free diet (GFD) in patients with asymptomatic biopsy confirmed CD and T1D. Patients (ages 8–45) will be randomly assigned to a GFD or continue with their usual diabetes gluten containing meal plan [27] (Fig. 2 study flow diagram). Patients will be followed-up every 3 months where Visit 1 is randomization, Visits 2,3,4 and 5 as 3, 6,9, and 12 months respectively from randomization. We anticipate that this may be a challenge as adherence to dietary advice is reported to be the lowest of all treatment types [28] with a range of 36-96 % as strict adherence [15].

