### Dietary adherence

Dietary adherence will be assessed at each visit following the baseline visit. Adherence assessment will be classified as objective and subjective as described earlier.

Subjective and objective assessment of adherence will include food records collected at visits 1, 3 and 5 (randomization, 6 and 12 months) and a typical day intake at visits 2 and 4 (3 and 9 months) for both groups. All records will be evaluated for inclusion and exclusion of gluten. In addition, food records will be analyzed via ESHA, dietary food processor. GI/ GL and gluten content will be assessed at baseline, 6 and 12 months in both arms. For the intervention group, the adherence to GFD will be further assessed by the application of the Celiac Dietary Adherence Test (CDAT). Additionally, TTG-IgA titers will be measured at 6 (Visit 3) and 12 months (Visit 5) visits to asses GFD/GCD compliance.

After randomization (visit 1) at visits 2 to 5, both study groups, intervention and control, will be interviewed to assess and document adverse events including severe hypoglycemia requiring assistance, hospitalization, any changes in non-insulin medications, supplements and vitamins from previous visit. HbA1c and TTG will be collected at visits 1, 3 and 5 for both arms. GISS and CDAT questionnaires will also be completed only for intervention group, at each visit.

A trained dietitian from the leading site will train identified dietitians from the partner sites using standardized educational material and a detailed manual of operations describing the goals objectives of the dietary curriculum and the steps for the dietary interview at each visit. The standardized tools will be used to maintain quality and consistency of dietary education and collection of information.

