#### Intervention group

Visit 1: The dietary interview will consist of a comprehensive nutritional assessment followed by the GFD education. “Your Guide to Well-being: Managing Celiac Disease and Diabetes” is a resource manual, divided into modules, that was specifically designed for this population to address the complex dietary nature of living with both CD and T1D. This resource as well as "Pocket Dictionary of Ingredients" and 'Checking Ingredient List' by the Canadian Celiac Association will be provided to the participants along with the GFD education. Participants will be directed to online resources such as Apps that will help and guide them in determining presence of gluten in food, as well as locations of gluten free restaurants and stores in their vicinity. At the end of the education session an assessment will be carried out using food labels for the comprehension of the GFD, carb counting skills and current diabetes management. Three day food records will be collected, clarified and sent to central analysis for ESHA (Elizabeth Stewart Hands and Associates) processing.

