#### Control group

Visit 1: The dietary interview will consist of a comprehensive nutritional assessment including on how well the subjects are managing their current diet and ensuring consumption of GC foods. Food labels will be used to assess carbohydrate counting skills. Three day food records will be collected, clarified and sent to central analysis for ESHA processing.

A 4 week follow-up call will be done in both groups to support, address questions and concerns, document any changes in non-insulin medications, supplements and vitamins and document adverse events including severe hypoglycemia requiring assistance.

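### Baseline diet is assessed with the allocation known and in interviews that differ by arm, leaving record clarification and fallback recall open to arm-dependent bias

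*Protocol article*

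**What the plan says.** All references are to the protocol article.

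- **Timing.** The section on dietary assignment in a clinical trial sets the schedule: "Visit 1 is randomization, Visits 2,3,4 and 5 as 3, 6,9, and 12 months respectively from randomization". The Dietary adherence section places the first food record at the same visit: "food records collected at visits 1, 3 and 5 (randomization, 6 and 12 months".
- **Forms.** Under Dietitian visits: "Worksheets specific to each arm and visit have been designed to ensure consistent collection of information". The sentence goes on to promise uniform parameters for both assessing and teaching. The dietitian completes the worksheets at every visit, which includes visit 1.
- **Visit 1, GFD arm.** The interview is a "comprehensive nutritional assessment followed by the GFD education". A label-based comprehension check closes the education session. The last sentence of the paragraph has the 3-day record collected, clarified and forwarded for analysis.
- **Visit 1, control arm.** The interview is a "comprehensive nutritional assessment including on how well the subjects are managing their current diet and ensuring consumption of GC foods". Labels are used to check carbohydrate counting, and the paragraph ends with almost the same sentence about the record.
- **Fallback.** Under Subjective measures of assessment: "In the absence of a 3 day food record a typical day recall will be taken".
- **Common elements.** Dietitian visits has every participant complete the same 3-day record for visit 1 and applies the Osborne formula to everyone at baseline. Dietary adherence has glycemic index (GI), glycemic load (GL) and gluten assessed at baseline, 6 and 12 months in both arms.

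**The concern.** Once a diet has been assigned, neither participant nor dietitian can be blinded to it. Baseline is the one dietary assessment that can be completed without knowledge of the arm, and the described visit does not protect it. A dietitian who knows the arm, working from that arm's form, goes over the record with a participant who also knows the arm. Probing may then differ by arm, and so may what the participant adds or withdraws. The recall is more exposed than the record, because it is produced entirely within that visit.

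At stake are the dietary outcomes. The Background lists consumption patterns, GI and GL, and gluten quantification among them. Outcome assessments expects GI and GL to differ between arms and suggests that this may explain glucose variability. The Discussion plans to correlate adherence with gluten consumption. A baseline shifted by arm-dependent questioning would blur any reading of dietary change from baseline.

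**Working it through.** The article gives no figure to reproduce, so the check compares its sections.

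**Step 1. Is the allocation known at the baseline interview?** Visit 1 is the randomisation visit, the baseline record is collected there, and the dietitian fills in an arm-specific form there. An arm-specific form cannot be selected, nor an arm-specific interview held, before the arm is known. As written, the answer is yes.

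**Step 2. What is common and what differs at visit 1?**

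| Element | GFD arm | Control arm | Same? |
|---|---|---|---|
| Record form | 3-day record | 3-day record | Yes |
| Nutrient analysis | Central, ESHA | Central, ESHA | Yes |
| Baseline gluten | Osborne formula | Osborne formula | Yes |
| Baseline GI and GL | Calculated | Calculated | Yes |
| Worksheet | GFD version | Control version | No, though uniform parameters are stated |
| Interview content | Assessment, then GFD teaching and label check | Assessment that includes ensuring gluten intake; carbohydrate-counting check | No |
| Recall if no record | Taken with arm known | Taken with arm known | Same tool, different interview context |

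**Step 3. Is the record clarified after the GFD teaching?** The article does not settle this. In the GFD paragraph the assessment is explicitly placed before the teaching, and the label check at the end of the teaching. The sentence on the record comes last but has no word tying it to that sequence. It also comes last in the control paragraph, where there is no GFD teaching.

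**Step 4. What could move?** Objective measures of assessment gives:

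gluten = 0.8 × plant protein from overt gluten sources.

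Each gram of such protein added or dropped at clarification or recall changes the estimate by 0.8 × 1 g = 0.8 g. GI, GL and nutrients likewise depend on the foods and portions finally listed. Dietitian visits assigns the Osborne formula to all subjects at baseline and the 20 ppm standard to the GFD arm, so baseline is the clearest like-for-like gluten comparison between arms.

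**Step 5. What cannot move?** HbA1c and TTG are blood measures. The primary ANCOVA adjusts for baseline HbA1c, age group and site, and not for baseline diet.

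**Step 6. How large is it?** The enrolment target is 200, and every participant passes through visit 1. The article does not give the share without a 3-day record, or how far clarification changes a record. No bias can be calculated.

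**The case against.** A reader might infer that baseline diet is measured differently in the two arms, or that GFD participants clarify their record fresh from being taught where gluten is found. The documents do not support either reading. The form, the central analysis and the baseline gluten formula are shared. The worksheet sentence itself promises uniform parameters. The GFD assessment precedes the teaching, and the later position of clarification rests on sentence order alone. A record of two weekdays and one weekend day, completed for visit 1, cannot be produced within the visit, so it probably describes intake before any teaching. All of this stands, and it is why the point is limited to clarification and recall.

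Four further objections deserve an answer.

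- **The mechanism is weak.** The gluten formula uses overt sources, so someone who lists bread and pasta gets the same value with or without lessons on hidden gluten. This reduces the likely effect. It does not remove it, since items and portions can still be added, dropped or revised during probing. The article also does not say that the control arm's instruction to ensure gluten intake works as a prompt to report gluten foods; that it might do so is an inference.
- **The order of steps belongs in the manual of operations.** The article refers to such a manual, which is not shown, and practice may already be sound. But the article does more than stay silent: it states arm-specific forms and arm-specific content at the visit where baseline is taken.
- **The consequence is modest.** The statistics section specifies no change-from-baseline analysis of gluten, GI, GL or nutrients, and much of their use is descriptive. This is accepted and lowers the priority.
- **The trial is running.** It began in 2012 and is active at 16 centers, so a change would leave two baseline procedures in one dataset. This is accepted as a cost.

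**Conclusion.** The point holds in a limited form, as a cheap improvement. As described, baseline diet is assessed at the randomisation visit with the allocation known to both parties, on arm-specific worksheets and in interviews with different content. Clarification of the 3-day record, or the recall that replaces it, could therefore differ by arm. The possible effect is confined to baseline gluten, GI, GL and nutrients, and is greatest where a recall was used. Its direction and size are unknown. HbA1c, TTG and the primary analysis are unaffected.

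This rests on two assumptions: that sites follow the visit as the article describes it, and that the unseen manual of operations does not already complete baseline before the allocation is opened. It does not depend on clarification coming after the teaching.

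**What to change.** **Remaining enrolment.** At visit 1, complete the nutritional assessment, then collect and clarify the 3-day record (or take the recall), all on one worksheet common to both arms and before the allocation is opened. Begin the arm-specific interview content and education only after that. Keep the arm-specific worksheets for the rest of visit 1 and for visits 2 to 5.

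**Participants already enrolled.** Report by arm whether the baseline came from a record or a recall.

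If sites already work in this order, correct the Dietitian visits section and the two visit 1 descriptions to say so.

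**Cost.** One common form, a re-ordering within an existing visit, and brief retraining of site dietitians; no added visit or procedure. The allocation can be opened only once the baseline form is complete. Earlier participants will have been assessed under the previous procedure, so the date of change should be recorded at each site.

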### Height, weight, BMI and z-scores

Regular monitoring of anthropometric parameters will be performed to assess safety. Height and weight will be obtained at every clinic visit and BMI and z-scores will be derived from those measurements. Level of activity will be ranked as per The Canadian Physical activity guidelines (www.csep.ca/) (Fig. 1).

### Dietary adherence

Dietary adherence will be assessed at each visit following the baseline visit. Adherence assessment will be classified as objective and subjective as described earlier.

Subjective and objective assessment of adherence will include food records collected at visits 1, 3 and 5 (randomization, 6 and 12 months) and a typical day intake at visits 2 and 4 (3 and 9 months) for both groups. All records will be evaluated for inclusion and exclusion of gluten. In addition, food records will be analyzed via ESHA, dietary food processor. GI/ GL and gluten content will be assessed at baseline, 6 and 12 months in both arms. For the intervention group, the adherence to GFD will be further assessed by the application of the Celiac Dietary Adherence Test (CDAT). Additionally, TTG-IgA titers will be measured at 6 (Visit 3) and 12 months (Visit 5) visits to asses GFD/GCD compliance.

After randomization (visit 1) at visits 2 to 5, both study groups, intervention and control, will be interviewed to assess and document adverse events including severe hypoglycemia requiring assistance, hospitalization, any changes in non-insulin medications, supplements and vitamins from previous visit. HbA1c and TTG will be collected at visits 1, 3 and 5 for both arms. GISS and CDAT questionnaires will also be completed only for intervention group, at each visit.

A trained dietitian from the leading site will train identified dietitians from the partner sites using standardized educational material and a detailed manual of operations describing the goals objectives of the dietary curriculum and the steps for the dietary interview at each visit. The standardized tools will be used to maintain quality and consistency of dietary education and collection of information.

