**Methods and design:**

The CD-DIET Study (Celiac Disease and Diabetes - Dietary Intervention and Evaluation Trial) is a multicenter randomized controlled trial aimed at evaluating the safety and efficacy of a GFD in patients with asymptomatic celiac disease and T1D on key diabetes and patient-centered outcomes.

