## Background

Celiac Disease (CD) is an autoimmune disease characterized by damage to the small intestine, triggered by gluten ingestion from wheat, rye and barley and their derivatives in genetically susceptible individuals [1, 2]. Currently the only treatment for CD is a lifelong adherence to the gluten-free diet. CD prevalence in T1D patients approximates 5-7 %. Despite this increased risk, many health care professionals struggle as to the optimal approach to managing CD in Type 1 Diabetes (T1D). The diagnosis of patients who present with symptomatic CD, including malabsorption and obvious pathology upon biopsy, remains straightforward, with improvements noted on a gluten-free diet. Many patients identified by screening, however, tend to be asymptomatic [3, 4]. Evidence is inconclusive as to whether the benefits of screening and potentially treating asymptomatic individuals outweigh the harms of managing a population already burdened with an established chronic illness.

The CD-DIET Study (Celiac Disease and Diabetes - Dietary Intervention and Evaluation Trial) is a multicenter randomized controlled trial aimed at evaluating the safety and efficacy of a GFD in patients with asymptomatic celiac disease and T1D over 1 year. Key outcomes include the impact of GFD on diabetes control (HbA1c), bone health, blood glucose variability, and patient centered measures including quality of life and self-perceived health. Dietary outcomes will include description and evaluation of food consumption patterns including glycemic index and load, dietary characteristics including gluten quantification, and highlight objective and subjective measures of GFD adherence. As a consequence, a de-novo dietary curriculum specifically addressing the educational requirements for GFD and T1D was developed to study dietary adherence and facilitate evaluation of key dietary components and their impact on study outcomes (Fig. 1).

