**Fig. 3 Fig3:**
[figure not shown]
methods of Assessment for GFD/GCD arms

A 3 day food record will be collected and clarified. Subsequently, records will be sent to central analysis where nutrient intake will be analyzed using the computer based ESHA food processor which contains a wide data base capable of analyzing over 160 food nutrient components and compare to DRIs. The analysis will include macronutrient distribution to be compared to CDA practice guidelines and specific nutrients including calcium, iron, vitamin D and fiber. Alterations in macronutrients, vitamins and minerals have been associated with imbalances and/or deficiencies with the GFD [5–8]. Additionally, Glycemic index (GI) and glycemic load (GL) of mixed meal will be calculated and analyzed for both GFD and GCD.

In this study we are also planning to describe the food consumption patterns of our population with dietary gluten. This will be done by multiplying the plant proteins of overt gluten sources by a factor of 0.8 [29]. This is a relatively novel approach in North America in relation to its application to dietary intake. Our findings from a previous study show that this approach to dietary gluten estimation is reasonable and valid (29). Dietary gluten for the GFD group will be estimated by using the maximum 20 ppm standard as defined by Health Canada’s labelling regulations [30].2.Celiac dietary Adherence Test (CDAT)- a 7 item questionnaire that has been demonstrated to have a highly predictive value (88 %) for verifying compliance with the GFD in adults, as compared to TTG IgA and dietary evaluation [31]. It will be administered to the subjects randomized to the GFD at every visit after randomization (visits 2–5) (Fig. 4).

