### Changes in dietary intervention assignment (cross-overs)

In cases of symptom presentation as defined by Mahmud et al. [28] subjects will be crossed over into the GFD.

Power calculation and statistics:

The outcome measure used to calculate sample size will be the change in HbA1c level from baseline to month 12. Based on previous work, in a non-randomized comparison of HbA1c levels over time in type 1 diabetes patients with asymptomatic CD who received a GFD versus patients with type 1 diabetes alone, an increase in HbA1c of 8.3 ± 1.1 % to 8.9 ± 1.5 % was observed.10 As such, 91 evaluable individuals per group are required to provide 80 % power to detect a difference of at least 0.5 % at the 0.05 level of significance. The enrolment of 200 participants will allow for a non-evaluable rate of about 10 %. To reach the recruitment target of 200 individuals, approximately 5000 patients with an established diagnosis of type 1 diabetes will be screened for asymptomatic CD. Efficacy analyses will be performed on the intent-to-treat population consisting of all randomized participants.

The primary efficacy outcome, the change in HbA1c at 12 months, will be analyzed using an analysis of covariance (ANCOVA) model that includes adjustment for baseline HbA1c, age groups and investigative sites. Treatment effect will be quantified using the point estimate, the two-sided 95 % CI, and associated p value. Significant effect will be declared at the 5 % significance level.

Severe hypoglycemic episodes over time will be analyzed as Poisson counts using the generalized estimating equations approach to account for correlation among repeated measures within an individual. The QOL data over time will be analyzed by means of a linear mixed effects model including factors for treatment, investigative sites, age groups, and baseline QOL scores. BG variability and change in Z-score at the lumbar spine will be analyzed using the ANCOVA approach. The Statistical Analysis System (SAS) procedures GENMOD, MIXED and GLM in SAS V.9.2, will be used to perform the respective analyses.

Patient consent: Obtained.

Ethics Approval: Research Ethics Board Hospital for Sick Children, University of Toronto and at all recruitment sites.

The CD-DIET study data safety and monitoring board will perform regular reviews of collected safety and efficacy data. The protocol was peer reviewed by the JDRF.

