## Abbreviations

CCA: Canadian Celiac Association
CD: Celiac Disease
CDA: Canadian Diabetes Association
CDAT: Celiac Dietary Adherence Test
CD-DIET Study: Celiac disease and Diabetes- Dietary **I**ntervention and Evaluation Trial
CPG: Clinical Practice Guidelines
GCD: Gluten containing diet
GFD: Gluten free diet
GISS: Gastrointestinal symptom scale
HbA1c: Glycosylated hemoglobin
PedsQL: Pediatric Quality of Life
QOL: Quality of life
SDE: Standardized Dietitian Evaluation
T1D: Type 1 Diabetes
TTG: Tissue Transglutaminase antibodies
TTG - IgA: Tissue Transglutaminase IgA Antibody Assay

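### The gastrointestinal symptom scale is completed only in the GFD arm and no equivalent is named for controls, although symptom presentation is what moves controls onto the GFD

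*Protocol article*

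**What the plan says.** Protocol article, *Dietary adherence*: "GISS and CDAT questionnaires will also be completed only for intervention group, at each visit". The *Abbreviations* list gives "GISS: Gastrointestinal symptom scale".

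On CDAT, the text under *Objective measures of assessment* (following Fig. 3) agrees with the one-arm rule: "It will be administered to the subjects randomized to the GFD at every visit after randomization (visits 2–5").

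On crossover, *Changes in dietary intervention assignment (cross-overs)* begins "In cases of symptom presentation as defined by" a cited paper, and states that "subjects will be crossed over into the GFD".

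For both arms, *Dietary adherence* provides that at visits 2 to 5 "both study groups, intervention and control, will be interviewed to assess and document adverse events including severe hypoglycemia requiring assistance", together with hospital admissions and changes in other medication and supplements. *Control group* (Visit 1) adds a telephone call at four weeks to both arms that also records adverse events.

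The aim in *Background* is "evaluating the safety and efficacy of a GFD in patients with asymptomatic celiac disease and T1D over 1 year".

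**The concern.** Participants are enrolled because they have no symptoms. Whether those who stay on gluten develop symptoms, and whether those on the GFD do, is relevant to a trial of safety and efficacy. The only symptom scale that the article names is used in the arm where a symptom-driven switch changes nothing, and is withheld from the arm where it changes the diet.

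Two things are at stake. There will be no randomised comparison of GISS. And the arms will differ in how hard symptoms are looked for: one is prompted by a scale at each visit, the other only by a general interview. Participants and dietitians know the assigned diet, so a later difference in reported symptoms could reflect the questioning as much as the diet.

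**Working it through.** The plan states no figure on this point, so the check sets the texts side by side.

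1. **Is the restriction explicit?** Yes. The sentence in *Dietary adherence* says *only*, which excludes controls. It is a stated collection rule, not a detail lost when the protocol was condensed into an article.

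2. **Does the reason for restricting CDAT carry over to GISS?** No. CDAT asks about compliance with a diet that controls are not following. GISS, by its expanded name, asks about symptoms. *Components dietary assessment and adherence* lists three adherence components (dietary interview, CDAT, serology), and GISS is not among them. The article gives no reason for pairing the two questionnaires.

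3. **In which arm does the symptom trigger act?** The consequence of symptom presentation is a move to the GFD. A participant randomised to the GFD is already assigned to it, so the rule can change assigned treatment only for controls.

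4. **What symptom measurement do controls have?** *Dietitian visits*, *Dietary adherence*, the control-group visit descriptions and the conditional month-7 call were compared. They give controls the dietary interview, self-report on the diet, serology, and the adverse-event and medication interview. None names a symptom scale. Figs. 1 and 4 (outcomes and visit components) are not shown, so they can neither confirm nor contradict this.

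5. **How much is not collected?** Inputs: 91 evaluable controls (*Power calculation and statistics*) and follow-up visits 2 to 5.
   - Follow-up scores absent: 91 × 4 = 364.
   - With a visit 1 score: 91 × 5 = 455.
   - Control scores available for a between-arm GISS contrast: 0.

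6. **Is there a GISS baseline even in the GFD arm?** Unclear. The sentence says each visit, but it follows text about visits 2 to 5, and CDAT is elsewhere limited to those visits.

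7. **Can the definition of the trigger be located?** The crossover section attaches reference 28 to it. *Dietary assignment in a clinical trial* uses 28 for the literature on adherence to dietary advice and 27 for the study design. The numbering looks inconsistent and should be checked.

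**The case against.** The strongest reply is that this article describes the dietary curriculum and points elsewhere for the design. The trigger is defined in a cited paper, and how symptoms are elicited in controls may be set out there or in the manual of operations. Sites use worksheets specific to arm and visit, central training and standardised tools. Both arms have adverse-event interviews at visits 2 to 5 and a call at four weeks. The text of *Background* does not list gastrointestinal symptoms among the key outcomes, and the primary outcome is a laboratory value measured in both arms.

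Much of this stands, and it rules out three stronger readings that a reader might infer:

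- **That crossovers rest on unstandardised, unprompted or purely local reports, or cannot be audited.** The documents do not support this. The trigger has a cited definition that is not shown, controls are interviewed at every follow-up visit, and nothing says that crossovers go unrecorded.
- **That symptoms cannot be compared between arms at all.** Only GISS cannot. Adverse events are documented in both arms, although gastrointestinal symptoms are not named among the items.
- **That the GISS restriction costs power on HbA1c.** Controls who switch would dilute the intention-to-treat contrast, but that follows from the crossover rule, not from who completes GISS. The article gives no crossover rate, and adding GISS for controls would not restore power; it might even bring more symptoms to light. A power-loss figure would not measure this defect.

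What the reply does not answer is the sentence itself. It excludes controls in plain terms. A definition of the trigger is not a schedule for measuring symptoms, and an analysis plan cannot analyse scores that were never taken.

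**Conclusion.** The point holds in limited form. The article restricts a symptom scale to one randomised arm and names no equivalent for the other, while symptom presentation is what moves that other arm onto the GFD. The between-arm GISS contrast has no control data, and symptom ascertainment is unequal by design, with only the general adverse-event interview in common.

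This affects secondary and safety information. It does not enter the ANCOVA of HbA1c and does not threaten the primary result directly, so it should be fixed but is not critical. The conclusion assumes that the sentence in *Dietary adherence* reflects what is done at the sites and that the figures and documents not shown do not give controls the same scale. If they do, what remains is an error in the article.

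**What to change.** - Administer GISS to both arms at visit 1 and at visits 2 to 5, in the same form. Keep CDAT for the GFD arm, at visits 2 to 5.
- Report GISS by randomised arm under intention to treat, and record the GISS score at each crossover. Leave the crossover criterion unchanged.
- Reconcile *Dietary adherence* with the crossover section, and check the reference number attached to the symptom definition. If the full protocol already gives GISS to controls, correct the sentence in the article instead.
- Where control visits are already complete, report the GFD-arm scores as within-arm description only.

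**Cost.** One short existing questionnaire at visits that controls already attend. On the planned 200 participants, assuming equal allocation, that is 200 / 2 = 100 controls × 5 visits = at most 500 extra forms, plus an amendment. Scores for completed control visits cannot be recovered. The study began in 2012 and expected results by 2016, so that loss could be large. Asking controls systematically may also raise the number of symptoms they report, which should be borne in mind when visits before and after the change are compared.
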